### Control group

Women allocated to this group will be asked to continue their routine activities during the 16-week intervention period. They will be contacted every 2 months by telephone. The intervention will be offered to this group in three meetings during the 16 weeks of the intervention. The first meeting will focus on stretching exercise to be performed at home on a regular basis, a second meeting will be about self-esteem, and the last meeting will be about prevention of lymphedema. These meetings will occur with the purpose of promoting an environment where these women can talk and share their experiences with other women with breast cancer and make sure that they also receive health education information, because they will not receive the exercise intervention in the first phase of the study. These meetings were a requirement of the Ethics Committee of CEPON, a hospital that will take part in the study in Brazil, to ensure that the control group also receives possible benefits of the study. Likewise, this strategy can improve the adherence of the control group because they will feel like a group and create social bonds.

Both groups, the experimental (Pilates solo and belly dance) and control groups, will receive, after 16 weeks of the intervention, an explanatory booklet on the benefits of practicing physical activity after breast cancer diagnosis, as well as instruction on the prevention of lymphedema. As a strategy to improve adherence of the subjects in the trials, all of the patients will be invited to social meetings, social media groups, and thematic classes according to specific calendar dates (e.g., Carnival, Easter, Halloween, Christmas), and they will receive a T-shirt from the project at the first meeting. Additionally, direct contact with the subjects who miss a class will occur via text messages and phone calls. These activities are planned to make the subjects feel familiar with the trial environment. For the 2-year follow-up, the intervention and control groups will be invited to participate in a physical activity program organized by the university. They will also be contacted through social media and text message once per month to motivate them to practice physical activity and remind them of future data collection. After the end of the study, besides publication in academic journals, the main results will be presented at the hospital in Brazil and shared with the patients in brochure format. Figure 1 presents the participant selection process and the execution of the steps of the protocol.

### Assessment

#### Primary outcome measure

The main aim of the study is to evaluate the impact of a 16-week Pilates solo and belly dance protocol on quality of life (≥ 2% of the baseline scores) in patients with breast cancer undergoing clinical treatment. Quality of life is the primary outcome at all time points of the study, namely baseline; postintervention; and 6, 12, and 24 months after intervention. Quality of life will be the primary outcome because it involves all the physical and psychological aspects of the life of women with breast cancer. Therefore, the maintenance collection will take place considering the modification in quality of life and other outcomes that the Pilates solo and belly dance intervention can promote in these women.

The primary outcome of quality of life will be investigated by using the European Organization for Research and Treatment of Cancer Quality of Life Questionnaire C30 (EORTC QLQ-C30) [39]. This instrument was created by the European Organization for Research and Treatment of Cancer (EORTC) in 1986, and this is the third version. Validated for the cancer population by Michels et al. [40], with Cronbach’s α values of 0.72 for global health, 0.86 for the functional scale, and 0.81 for the symptomatic scale.

The instrument consists of 30 questions, being multidimensional and self-applied. Its objective is to evaluate the quality of life in patients with cancer in the last 4 weeks. It presents five functional scales (physical, functional, emotional, social, and cognitive), a scale on global health status, three symptom scales (fatigue, pain, and nausea/vomiting), and six additional symptom items (dyspnea, appetite, constipation, diarrhea, and financial difficulties). The answers are presented in the form of a Likert scale following the classification 1 = not at all, 2 = a little, 3 = quite a bit, and 4 = very much. The only exception applies to the global health scale. This is composed of two questions that ask the patient to rate both health and quality of life in the last week according to grades of 1 to 7. In this case, 1 would be a poor quality of life and 7 a good quality of life.

The EORTC QLQ-C30 is complemented by specific cancer modules. In this study, the breast cancer module, QLQ BR-23, validated for the Portuguese language by Michels et al. [40], with Cronbach’s α values of 0.78 and 0.83, will be used. The QLQ BR-23 consists of 23 questions incorporated into multi-item scales. It measures the functional scales (body image, sexual functioning, sexual enjoyment, and future perspective) and symptom scales (systemic therapy side effects, arm symptoms, breast symptoms, and upset by hair loss). Classifications are also in the range of 0 to 100, where values ​​closer to 100 for the functional scale indicate better patient functionality and values ​​closer to 100 for the symptom scales show higher presence of symptoms.

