**Methods:**

The participants will be allocated to either the intervention arm (Pilates solo or belly dance classes three times per week for 16 weeks) or a control group (receipt of a booklet on physical activity for patients with breast cancer and maintenance of habitual physical activity routine). The Pilates solo and belly dance classes will be divided into three stages: warmup and stretching, the main stage, and relaxation. Measurements of the study outcomes will take place at baseline; postintervention; and 6, 12, and 24 months after the end of the intervention (maintenance period). The data collection for both groups will occur with a paper questionnaire and tests covering general and clinical information. The primary outcome will be quality of life (EORT QLQ-C30 and EORT QLQ-BR23), and secondary outcomes will be physical aspects such as cardiorespiratory fitness (6-min walk test and cycle ergometer), lymphedema (sum of arm circumference), physical activity (IPAQ short version), disabilities of the arm (DASH), range of motion (goniometer test), muscular strength (dynamometer test) and flexibility (sit and reach test), and psychological aspects such as depressive symptoms (Beck Depression Inventory), body image (Body Image After Breast Cancer Questionnaire), self-esteem (Rosenberg), fatigue (FACT-F), pain (VAS), sexual function (FSFI), and sleep quality (Pittsburgh Sleep Quality Index).

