### Sample size

To calculate the sample size, the method of distinguishing between the means was used, being n = (α + β) 2 σ2/d2. The values of α = 0.05 and β = 0.80 were adhered to, for which, according to the Gaussian curve table, values of 1.64 and 0.84, respectively, were used. The difference between the means was obtained through the pilot study, and a variable considered for the calculation was quality of life, in which an average of the difference between all the scales in the before and after periods was found. This value of the expected selection was 6.15 ± 9.4. The expected variance (σ2) was 89.49. At the end of the analysis, after inclusion of a 30% margin of sample loss, a sample of 19 patients was selected for each group. Figure 1 shows the flow diagram of the study participants.

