#### Statistical analysis

First, a spreadsheet will be created using the Excel 2016 software (Microsoft, Redmond, WA, USA), from which the data will be transferred to IBM SPSS Statistics version 20.0 software (IBM, Armonk, NY, USA) for analysis. Descriptive statistics (mean, standard deviation, and percentage) for the characteristics of the sample will be computed. To investigate the relationship between general and health information of the control and experimental groups, chi-square or Fisher’s exact tests will be used. To analyze differences in the experimental and control groups in the baseline, postintervention, and maintenance periods, two-way analysis of variance with repeated measures and Holm-Šídák comparison tests will be conducted. Confounder variables will be considered in the analyses as type of treatment, type of surgery, age, and weight status. The analysis will be performed according to the protocol and intention to treat, meaning that all the patients will be evaluated according to the randomization process. Missing data will be handled using the multiple imputation method. The significance level of 5% will be two-sided.

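### Two whole questionnaires are primary at every visit with no score or deciding visit named, and the 2% target does not match the sample-size basis

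*Protocol article*

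**What the plan says.** All references are to the protocol article.

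- **Instruments.** The abstract (Methods) says "The primary outcome will be quality of life (EORT QLQ-C30 and EORT QLQ-BR23"; Table 3 also lists both questionnaires in the primary row.
- **Time points.** Primary outcome measure: "Quality of life is the primary outcome at all time points of the study". The sentence goes on to list baseline, postintervention, and 6, 12 and 24 months, so baseline is included. Table 3 adds a 3-month visit that this sentence, the abstract and Data collection do not have.
- **Scores.** The same section describes the content of the questionnaires. For QLQ-C30: "It presents five functional scales (physical, functional, emotional, social, and cognitive), a scale on global health status", then three symptom scales and six single items (five are listed). For BR-23: "It measures the functional scales (body image, sexual functioning, sexual enjoyment, and future perspective) and symptom scales", the latter being four. Higher is better on functional scales and worse on symptom scales.
- **Target.** The aim is given as an effect on "quality of life (≥ 2% of the baseline scores", with no further definition.
- **Sample size.** The planning value is 6.15 ± 9.4 points from the pilot, where "an average of the difference between all the scales in the before and after periods was found".
- **Analysis.** Statistical analysis plans a two-factor repeated-measures analysis of variance with Holm-Šídák comparisons at two-sided 5%, and adds: "The analysis will be performed according to the protocol and intention to treat". No score, visit or contrast is singled out.

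**The concern.** A primary outcome should be one quantity at one time, so that the trial gives one answer at a known error rate. Here the protocol fixes the opposite: both instruments and all time points are primary. Several results could each be reported as the primary one, and some could favour an intervention while others do not. Nothing in the text says which would decide.

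Three different quantities also stand in for the effect of interest: the questionnaires as a whole (outcome), at least 2% of baseline (target), and a pilot change averaged over all scales (sample size). A reader cannot tell what result would confirm the hypothesis, or whether the trial was sized for it.

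**Working it through.** **1. The plan's own figure.** Inputs from Sample size: z-values 1.64 and 0.84, variance 89.49, difference 6.15, loss 30%.

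n = (1.64 + 0.84)² × 89.49 / 6.15² = 6.1504 × 89.49 / 37.8225 = 14.55; 14.55 × 1.3 = 18.9, so 19 per group, as stated. The 6.15 is therefore the effect the trial was sized on, used in a one-sample (before-after) form.

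**2. Number of scores.** QLQ-C30: 5 functional + 1 global + 3 symptom scales + 6 items = 15. BR-23: 4 + 4 = 8. Total 23, or 22 if only the five listed items count.

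**3. Error across scores.** Assume Holm-Šídák protects perfectly within a score, so that each score costs one test at 5%, and that there is no true effect.

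- Independent scores: 1 − 0.95²³ = 0.69 (1 − 0.95²² = 0.68).
- Correlated scores, by simulation of three-group F-tests with 14 per arm and equal pairwise correlation (assumed values):

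| Correlation | 0 | 0.3 | 0.5 | 0.7 |
|---|---|---|---|---|
| 23 scores, at least one false positive | 69% | 58% | 46% | 32% |

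- About five grouped scores (for example three QLQ-C30 groupings and two for BR-23): 1 − 0.95⁵ = 0.23 if independent, falling to about 15% at the highest correlation.
- One pre-named score: 5%.

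**4. The 2% target in points.** Baseline scores are not given, so 50-80 is assumed on the 0-100 scale.

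- 0.02 × 50 = 1.0; 0.02 × 80 = 1.6 points.
- Against the planning value: 1.0/6.15 = 16%; 1.6/6.15 = 26%.
- The two cannot be the same target: 6.15/0.02 = 307.5, a baseline that a 0-100 scale cannot reach.
- Standard error of a difference between two groups, SD = √89.49 = 9.46: 9.46 × √(2/19) = 3.07 with 19 per group; 9.46 × √(2/14) = 3.58 with 14. The target is below both.
- For a symptom score of 0 at baseline, 2% is 0 points. No direction is stated for scales on which improvement is a fall.

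**5. The averaged planning quantity.** Of the 23 scores, 5 + 1 + 4 = 10 improve upward and 3 + 6 + 4 = 13 improve downward. As an illustration, if every score improved by 6.15 points and none were reversed, the average change would be (10 × 6.15 − 13 × 6.15)/23 = −0.80. Whether the pilot's average used reversed symptom scores is not stated, so the meaning of 6.15 cannot be recovered from the text.

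**The case against.** The strongest reply is that the protocol never says each scale will be tested as primary. It describes what the questionnaires contain. It also gives reliability for three QLQ-C30 groupings and two values for BR-23, and plans the sample size on one average, so fewer primary scores are possible. This stands: 22-23 is the upper reading of an unnamed score. It does not rescue the plan, because five grouped scores still give about 15-23%, and the single average is never declared as the outcome.

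Further inferences are tempting but unsupported:

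- *A false positive is more likely than not.* This fails for one test per score at correlations of 0.5 and above (46% and 32%), and the correlations are assumptions.
- *There are 23 × 4 × 2 = 184 uncontrolled contrasts.* This ignores Holm-Šídák, which addresses arms and visits within a score. Only the step across scores is uncontrolled.
- *Chance would meet the 2% target in about a third of trials per arm.* This needs a between-group decision rule that the protocol does not contain; testing is at two-sided 5%, and Statistical analysis does not use the 2%.
- *Two analysis sets are both primary.* The phrase on following the protocol and intention to treat can be read that way, but its own gloss describes analysis by randomized group only.

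The absence of a separate statistical analysis plan is no answer. The protocol positively states that all time points and both instruments are primary, so a later choice of one score would change the stated outcome.

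**Conclusion.** The point holds and should be settled before analysis. The primary outcome is not reduced to a score or a visit, baseline is wrongly listed as an outcome time, and no error control is stated across scores. The size depends on how many scores are treated as primary: about 32-69% for 23 scores over assumed correlations of 0.7 to 0, about 15-23% for five, and 5% only for one named in advance. These figures already credit Holm-Šídák with full protection within each score.

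The fault of the 2% target is separate from multiplicity. It does not say whether it applies to a patient, a group mean or a between-group difference, and it is inconsistent with the 6.15 points used for planning. Its size of 1.0-1.6 points rests on assumed baselines of 50-80. The comparison with a standard error of 3.1-3.6 points borrows the pilot's variance for an average over scales, which need not apply to any single scale.

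**What to change.** Before analysis, in the protocol and the registry entry:

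1. Name one primary score, for example QLQ-C30 global health status, or a defined summary with symptom scales reversed. Which one is the sponsor's choice.
2. Fix one time point, postintervention, and drop baseline as an outcome time.
3. Make the primary analysis intention to treat, each active arm against control, with Holm-Šídák over the two contrasts.
4. Make all other scores (including BR-23 unless it enters the named summary), the later visits and any per-protocol analysis secondary.
5. Delete the 2% target. State a between-group difference in points justified for the named score, and report the result with its confidence interval. Do not carry 6.15 over unless the named score is that average, with the handling of symptom scales stated, and the value is justified as a between-group difference.

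The cost is wording; no data collection changes. The small downside is that the other scales and visits lose primary status.

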#### Other outcome measures

As secondary outcomes, we will evaluate the physical and psychological variables associated with the quality of life. The physical outcomes are cardiorespiratory fitness, functional capacity, lymphedema, disabilities of the arm, ROM, strength, flexibility, and physical activity. In addition, the psychological outcomes are depressive symptoms, pain, fatigue, body image, self-esteem, sexual function, and sleep quality.

#### Cardiorespiratory fitness

To assess cardiorespiratory fitness, a submaximal incremental exercise test (85% of maximum heart rate [HRmax]) will be performed using a cycle ergometer (Excalibur Sport; Lode B.V., Groningen, the Netherlands). The protocol will start with a power of 20 W, and every 3 min, 15 W will be added, until the patient reaches 85% of HRmax, which will be identified through the equation (207 − 0.7 × age) [41]. In the initial 3 min of the test, the patient will be asked to remain in a resting position, accommodated by the cycle ergometer, to identify the values ​​of resting heart rate and oxygen consumption. Patients will be asked to maintain the rotation per minute (RPM) of the cycle ergometer always above 60 RPM. Expiratory gases and flow volume will be collected during the test and analyzed by using a calibrated metabolic system (Quark CPET; COSMED, Rome, Italy) to provide measurements of oxygen consumption. The heart rate will be monitored by a POLAR mark frequency and will be observed within the first 3 min of the test and at the end of each minute of the 3-min test stages. Also, every 3 min, the patient will be questioned about her perception of the exercise through the Subjective Perception Scale of Effort–Borg Scale [42]. This scale ranges from 6 to 20 points, where the sixth position would be the perception of “very easy” and 20 “exhausting.”

The 6-min walk test measures the distance a person can travel on a flat, rigid surface in 6 min. Its main objective is to determine tolerance to exercise and oxygen saturation during submaximal exercise [43]. Patients are asked to walk at their own pace as fast as possible during the 6 min, being allowed to walk slowly, stop, and/or rest when necessary and return to walking when they feel ready.

#### Lymphedema

The evaluation of lymphedema will be performed by calculating the arm volume, performed by measuring the circumferences of both upper limbs at five points distributed along the arm and forearm: at 21 cm and 11.5 cm above the olecranon to 7.5 cm, 14 cm, and 24 cm below the olecranon. The circumference will be obtained with the patient sitting, keeping the arm in abduction, flexed forearm, and hand resting on the chest. These measures are used to calculate the approximate volume of the five truncated cones formed at the points of circumference measurements. The sum of these five parts gives the total limb volume [44].

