#### Descriptive and control variables

The descriptive and control variables were divided into clinical variables (cancer stage, characteristics of treatment, previous clinical treatment, characteristics of surgical intervention, mammary reconstruction, date of surgery, presence of lymphedema, physiotherapy, and other diseases), sociodemographic variables (age, education, marital status, economic level, and occupation), and anthropometric measures (height and body mass). The descriptive and control variables will be acquired by self-report. The variables of the study regarding the Pilates solo and belly dance protocol are present in Table 3 and Fig. 2.

**Table 3 Tab3:** Study assessments

Outcomes	Instruments	Visits					
		Baseline	Postintervention	3-month	6-month	12-month	24-month
Primary							
Quality of life	European Organization for Research and Treatment of Cancer Quality of Life Questionnaire C30 (EORTC QLQ-C30) and Specific for Breast Cancer (EORTC QLQ-BR23)	√	√	√	√	√	√
Other outcomes							
Psychological							
Depressive symptoms	Beck Depression Inventory (BDI)	√	√	√	√	√	√
Pain	Visual analogue scale (VAS)	√	√	√	√	√	√
Fatigue	Functional Assessment of Cancer Therapy–Fatigue (FACT-F)	√	√	√	√	√	√
Body image	Body Image After Breast Cancer (BIBCQ)	√	√	√	√	√	√
Self-esteem	Rosenberg Self-Esteem Scale	√	√	√	√	√	√
Sexual function	Female Sexual Function Index (FSFI)	√	√	√	√	√	√
Sleep quality	Pittsburgh Sleep Quality Index	√	√	√	√	√	√
Physical							
Cardiorespiratory fitness	Cycle ergometer 6-min walk test	√	√	√		√	√
Lymphedema	Sum of the arm circumference	√	√	√	√	√	√
Physical activity	International Physical Activity Questionnaire (IPAQ–short version)	√	√	√	√	√	√
Disabilities of the arm	Disabilities of the Arm, Shoulder and Hand (DASH)	√	√	√	√	√	√
Range of motion	Goniometer test	√	√	√	√	√	√
Strength	Dynamometer test	√	√	√	√	√	√
Flexibility	Sit and Reach Test	√	√	√	√	√	√

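### Lymphedema is a limb volume in the Methods text but a sum of arm circumferences in the abstract and Table 3, and the volume rule counts five cones where its five points bound only four

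*Protocol article*

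**What the plan says.** Three places in the protocol article say how lymphedema is measured.

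- **Lymphedema section (Methods):** "The evaluation of lymphedema will be performed by calculating the arm volume". The inputs come from "measuring the circumferences of both upper limbs at five points distributed along the arm and forearm", located "at 21 cm and 11.5 cm above the olecranon to 7.5 cm, 14 cm, and 24 cm below the olecranon". They are turned into a volume as follows: "These measures are used to calculate the approximate volume of the five truncated cones formed at the points of circumference measurements". The total is then formed: "The sum of these five parts gives the total limb volume". A published method is cited for this rule, but it is not available here.
- **Abstract, Methods:** lymphedema is listed among the physical secondary outcomes with its measure in brackets, "lymphedema (sum of arm circumference".
- **Table 3 (Study assessments):** the instrument entered for lymphedema is "Sum of the arm circumference".

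The section Other outcome measures confirms that lymphedema is a secondary outcome, one of eight physical and seven psychological ones.

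**The concern.** There are two separate faults.

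1. **Two quantities carry one outcome name.** The Methods text adds cone volumes, whereas the abstract and Table 3 add circumferences. Brevity in the abstract does not explain this, because Table 3 is the assessment schedule and it sides with the abstract against the Methods text.
2. **The volume rule does not fit its inputs.** A truncated cone needs a circumference at each end. Five points therefore cannot give five cones, yet the section says five twice, once for the cones and once for the parts that are summed.

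What is at stake is the reporting of a named secondary outcome. The Background gives reduction of lymphedema as part of the reason for choosing Pilates. With two definitions open, either could be reported after the results are known, and the two do not carry the same information about a limb. An analyst who follows the volume rule literally also has to invent a fifth segment or drop one. Two analysts could do this differently.

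**Working it through.** **Inputs from the Lymphedema section.** Positions relative to the olecranon, with points above it negative: −21, −11.5, +7.5, +14 and +24 cm. The olecranon itself (0 cm) is not a listed point. Stated number of cones: 5.

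**Step 1: count the cones.** With k points along one limb there are k − 1 segments, so 5 − 1 = 4. The heights are:

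- 21 − 11.5 = 9.5 cm
- 11.5 + 7.5 = 19 cm (this segment spans the elbow)
- 14 − 7.5 = 6.5 cm
- 24 − 14 = 10 cm

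The total is 45 cm, which equals 21 + 24. The stated five cones are not reproduced.

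**Step 2: what would give five.** Five cones need a sixth circumference. If it were taken at the olecranon, the 19 cm segment would split into 11.5 and 7.5 cm, and the heights would be 9.5, 11.5, 7.5, 6.5 and 10 cm. The text lists no such point.

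**Step 3: how much the cone count matters (illustration).** The volume of a truncated cone with end circumferences C1 and C2 and height h is V = h(C1² + C1·C2 + C2²)/(12π). The documents give no circumferences, so assume 33, 30, 26, 23 and 17 cm from the upper arm downward.

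- Four cones: 750.7 + 1187.4 + 310.9 + 320.7 = about 2570 mL.
- Five cones, with an assumed olecranon circumference of 25 cm: about 2464 mL (−4.1%).
- Five cones, with an assumed olecranon circumference of 29 cm: about 2631 mL (+2.4%).

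**Step 4: whether sum and volume are interchangeable (illustration).** Take three assumed arms with the same circumference sum:

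| Circumferences (cm) | Sum (cm) | Four-cone volume (mL) |
|---|---|---|
| 33, 29, 25, 24, 18 | 129 | 2496 |
| 33, 30, 26, 23, 17 | 129 | 2570 |
| 33, 31, 27, 22, 16 | 129 | 2649 |

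The sum cannot tell these arms apart, but the volumes differ by up to 2649 − 2496 = 153 mL, or about 6% of the smallest.

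The two measures can also move in opposite directions. Start from the middle arm, add 2 cm at 11.5 cm above the olecranon and take 3 cm off at 24 cm below it (33, 32, 26, 23, 14). The sum falls from 129 to 128 cm, while the four-cone volume rises from about 2570 to about 2663 mL (+3.6%).

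**The case against.** The strongest reply is that little turns on this. Lymphedema is one of fifteen secondary outcomes, and neither the quality-of-life endpoint nor the sample size depends on it. Any single rule would apply equally to all arms and visits. On the assumed limb, adding an elbow point shifts the volume by only a few percent. All the circumferences used above are assumed, and nothing shows that the treatment groups would be ordered differently under the two measures. These points stand and they limit the weight of the finding. They do not remove it, because the document states one outcome in two incompatible ways and gives a rule that cannot be carried out. That is different from detail left to a fuller document.

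A reader might also infer more than the text supports:

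- **That lymphedema cannot be computed at all.** This is too broad. The sum of five circumferences is computable, and so is a four-cone volume. Only the five-cone volume in the Lymphedema section is not.
- **That four cones is the right correction.** The documents do not show whether five is a miscount or whether a sixth circumference is taken but not listed. A point at the olecranon would give exactly five segments, and the cited method is not at hand to settle it.
- **That the plan is wrong not to define the outcome as affected minus unaffected arm.** Both limbs are measured. How they are combined is a detail that an article may leave to the full protocol or the analysis plan. The eligibility criteria also do not exclude bilateral disease, in which there is no unaffected arm.
- **That change in body weight is ignored.** The Statistical analysis section names weight status among the confounders to be considered. Whether that covers weight change during the trial is open, but weight is not unaddressed.

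**Conclusion.** The point holds in two parts, both of which can be checked from the protocol article alone. First, the Methods text on one side and the abstract and Table 3 on the other define lymphedema as different quantities in different units. Second, the five listed points bound four truncated cones, so the five-cone volume cannot be obtained from the listed measurements.

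The count of cones is exact and rests on no assumption. The sizes are illustrations on assumed arms: a volume range of about 6% at an identical circumference sum, and a shift of −4.1% to +2.4% if an olecranon point of 25 to 29 cm were added. They show that the measures are not interchangeable. They do not estimate any effect on the trial's result. The consequence is confined to a secondary outcome.

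**What to change.** Before analysis, choose one lymphedema measure and name it identically in the abstract, the Lymphedema section and Table 3. If the other is also reported, label it supportive.

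If volume is kept, make the points and segments agree in one of two ways, according to what is actually measured:

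- state four truncated cones with heights 9.5, 19, 6.5 and 10 cm, and change both mentions of five cones or parts to four; or
- if a sixth circumference is in fact taken, for example at the olecranon, add it to the list of points and keep five cones.

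The sponsor needs to confirm which of these describes the measurements being made. The cost is wording only if no sixth point is needed or it is already being recorded. Otherwise it is one more tape measurement per arm at each visit, and visits already completed would lack it. The primary outcome and sample size need no change.
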